### Analysis

To begin analysis, we will perform descriptive statistics of all variables used in the analysis, using means, SDs and Student's t-tests for normal, continuous variables; medians, IQRs and Mann-Whitney tests for non-parametric, continuous variables; and proportions and χ^2^ tests for categorical variables. We will explore and report differences between patients with follow-up surveys at 30-days compared with non-responders.^26^ Among patients included in the analysis, we will also explore and report differences between those with complete records versus those with missing data. For variables with missing data, we will perform multiple imputation where appropriate.

Our first aim is to describe the characteristics of postoperative falls in an unselected surgical population, such as their occurrence, timing, injuries and risk factors. To achieve that goal, we plan to perform the following analyses:
Descriptive statistics:
Per cent who fell while still in the hospital;Number of falls (0, 1, 2, 3+) and fall rate in the 30 days and 1-year following surgery;Fall rate and per cent who fell by surgery type (10 surgery departments);Injuries from falls in the 30 days following surgery;Injuries from falls in the 1 year following surgery.▸χ^2^:
Proportion with any injury, comparing preoperative falls to postoperative falls at 30 days and 1 year;Proportion with severe injury, comparing preoperative falls to postoperative falls at 30 days and 1 year.Risk factors: see results from logistic regression model in Aims 2a–c.

As a subaim of Aim 1, we also plan to explore the rate of falls in the short-term versus long-term postoperative periods. To accomplish this, we will calculate the rate of falls per 100 person-years in the Behavioral Risk Factor Surveillance System (BRFSS) system, which serves as the control rate of falling in the general population of adults in the USA. We will then convert the 30-day, 6-month and 1-year fall rates from the SATISFY-SOS population into falls/(100 person-years) using the BRFSS distribution. Finally, we will compare the observed rate of falling to the general population's rate of falling at 1 month and 1 year (Student's t-test) to estimate how the rate of falls changes after surgery.

Aim 2 explores whether a preoperative history of falls serves as a useful tool for predicting surgical outcomes. First, we will calculate a crude dose–response relationship between the number of falls at baseline (0, 1, 2, 3+) and each outcome (postoperative falls, postoperative functional dependence, postoperative quality of life, in-hospital complications and 30-day readmission). For comparison, we will also calculate the crude dose–response relationship for a falls and injuries composite scale.^27^ We will examine the bivariate relationship between preoperative falls and each complication subcategory (heart/stroke, lung, blood clots, kidney/intestine, nerve injury, infection, delirium or other) using χ^2^ tests for the purpose of hypothesis generation.

To assess the relationship after controlling for important confounders, we will use logistic regression (categorical outcomes) and linear regression (continuous outcomes). Specifically, we will use forced entry of all prespecified variables. We will check all models for linearity of logit, multicollinearity, influential cases, conformity to linear gradients and goodness of fit. Since the number of possible interaction terms is large (between 45 and 91 per model), including all of them creates an unacceptably large risk of type I error. Therefore, our statistical consultant ([name]) recommended selecting only 10% of the most clinically relevant interaction terms. Using a combination of prior research and clinical judgement, two investigators ([name] and [name]) selected the 10% most clinically relevant interaction terms for each model. The online supplementary material contains these prespecified interaction terms. Non-significant interaction terms (p>0.01) will be removed from the model.

10.1136/bmjopen-2016-011570.supp8Supplementary data

Each model will include the following demographic and explanatory variables: age, sex, race (white vs non-white), BMI, preoperative falls history (0, 1, 2, 3+), Charlson Comorbidity Index (≥3 vs <3), American Society of Anesthesiology (ASA) physical status (≥3 vs <3) and procedural cardiac risk. On the basis of a careful literature search of each outcome variable (see the Literature search and review section), we selected confounding variables that are both routinely collected and known at the time of surgery planning. Outcome variables and their corresponding outcome-specific confounders are listed below.
Presence or absence of at least one fall in the 30 days (primary outcome) and 1 year following surgery:
Physical activity level (<4 vs >4 metabolic equivalents (METs));Baseline altered elimination (bowel or bladder);Baseline mobility abnormality;Dizziness/vertigo;Depression.▸Barthel Index that is worse than baseline, at 30 days and 1 year after surgery:
Baseline Barthel Index score;Neurological impairment;Mood disorder (depression or anxiety);Smoking status.▸Physical quality of life score, at 30 days and 1 year after surgery:
Baseline physical quality of life score;Preoperative physical activity level (<4 vs >4 METs);Chronic pain;Mood disorder (depression or anxiety);Smoking status.▸Mental quality of life score, at 30 days and 1 year after surgery:
Baseline mental quality of life score;Chronic pain;Mood disorder (depression or anxiety).▸Presence or absence of any complication that occurred in the hospital, as reported in the 30-day survey:
Smoking status.▸Presence or absence of readmission at 30 days, as reported in the 30-day survey:
In-hospital complications (30-day survey);Incontinence.

After running each model, we will substitute the number of falls (0, 1, 2, 3+) explanatory variable for the falls and fall injuries composite scale^27^ to evaluate which scale better predicts outcomes. Since we test multiple hypotheses, the threshold for significance will be α=0.01. We will report results using ORs and 99% CIs, along with variance estimates for regression parameters.

Using SAS/STAT software, V.9.4 (SAS Institute, Cary, North Carolina, USA), [name] will perform all analyses. Analysis will begin only after acceptance of this protocol for publication. This approach reassures readers that key analyses were truly prespecified rather than post hoc. If the authors decide to perform post hoc analyses, these will be described as such and will be performed for the purpose of further hypothesis generation.

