## Specific aims

*Aim 1*: Describe characteristics of postoperative falls in an unselected surgical population, including their rate, timing, associated injuries and risk factors.

We hypothesise that the occurrence, injuries and risk factors of postoperative falls will be similar to those of preoperative falls, and the rate of postoperative falls will decline from 30-days after surgery to 1 year after surgery.

*Aim 2a*: Determine whether a preoperative history of falls serves as a useful tool for predicting falls in the 30 days (primary outcome) and 1 year following surgery of all types.

*Aim 2b*: Determine whether a preoperative history of falls predicts patient-centred outcomes including functionality and quality of life at 30 days and 1 year after surgery (secondary outcomes).

*Aim 2c*: Replicate findings that a preoperative history of falls predicts in-hospital surgical complications and readmission at 30 days (secondary outcomes).

We hypothesise that a history of preoperative falls will predict poor postsurgical outcomes, including postoperative falls, functional dependence, poor quality of life, in-hospital complications and readmission.

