Table 1 contains all variables to be collected for the study, along with the form of the variable, its source, time point for collection and whether or not it comes from a standardised tool. Of note, the informaticist performs rigorous data validation on each queried variable. If continuous variables are found to exhibit non-linearity, they will be categorised in accordance with their distribution.

**Table 1 BMJOPEN2016011570TB1:** Characteristics of all variables used in this study

Type	Variable name	Form	Source	Time	Use of standardised tool
Explanatory	Preoperative falls	0, 1, 2, 3+	Survey	BL	Yes^21^
	Charlson Comorbidity Index	Ordinal, 0–12	CPAP H&P	BL	Yes^29^
	ASA physical status	Ordinal, 1–6	Anaesthesia record	Surgery	Yes^30^
	Procedural cardiac risk	Ordinal, 5 categories from high to low	CPAP clinician	BL	Yes^31^
Outcome	Postoperative falls	Binary (V.2); 0, 1, 2, 3+ (V.3)	Survey	30 days, 1 year	Yes^21^
	Functional dependence	Ordinal, 0–100 by 5	Survey	30 days, 1 year	Yes^32^
	Physical quality of life	Continuous, 0–100	Survey	30 days, 1 year	Yes^33^ ^34^
	Mental quality of life	Continuous, 0–100	Survey	30 days, 1 year	Yes^33^ ^34^
	In-hospital complications	Dichotomous	Survey	30 days	No
	Readmission	Dichotomous	Survey	30 days	No
Demographic	Age	Continuous	Medical record	BL	NA
	Sex	Dichotomous	Medical record	BL	NA
	Race	Nominal	Medical record (patient report)	BL	NA
	Ethnicity	Hispanic/Latino or not	Medical record (patient report)	BL	NA
	Body mass index	Continuous	CPAP nurse	BL	Yes
Confounder	Functional dependence	Ordinal, 0–100 by 5	CPAP nurse	BL	Yes^32^
	Physical quality of life	Continuous, 0–100	Survey	BL	Yes^33^ ^34^
	Mental quality of life	Continuous, 0–100	Survey	BL	Yes^33^ ^34^
	Smoking status	Current, past, never	CPAP physician or nurse	BL	NA
	Physical activity level	<4, 4–6, 6–10, >10 (METs)	CPAP physician	BL	Yes^35^
	Incontinence	Dichotomous (any issue)	CPAP nurse	BL	Yes^32^
	Toileting difficulty	Dichotomous (any issue)	CPAP nurse	BL	Yes^32^
	Mobility issue	Dichotomous (any issue)	CPAP nurse	BL	Yes^32^
	Neurological impairment (stroke, paraplegia or quadriplegia, Parkinson disease or multiple sclerosis)	Dichotomous	CPAP H&P	BL	No
	Chronic pain	Dichotomous	CPAP physician ROS	BL	No
	Dizziness/vertigo	Dichotomous	CPAP physician ROS	BL	No
	Depression	Dichotomous	CPAP H&P	BL	No
	Anxiety	Dichotomous	CPAP H&P	BL	No
Descriptive	Fall-related injury	Check all that apply	Survey	BL, 30 days, 1 year	No

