	Days from BL to 30 days survey	Continuous	BL survey, Press Ganey	BL completion date to 30 days process date	NA
	Days from BL to 1 year survey	Continuous	BL survey, Press Ganey	BL completion date to 1 year process date	NA
	Surgery type	10 categories	Medical record	BL	NA
	In-hospital falls	Dichotomous	Survey (V.3 only)	30 days	Yes^21^
	In-hospital heart problem or stroke	Dichotomous	Survey	30 days	No
	In-hospital lung complication	Dichotomous	Survey	30 days	No
	In-hospital blood clot	Dichotomous	Survey	30 days	No
	In-hospital kidney or intestine complication	Dichotomous	Survey	30 days	No
	In-hospital nerve injury	Dichotomous	Survey	30 days	No
	In-hospital infection	Dichotomous	Survey	30 days	No
	In-hospital delirium	Dichotomous	Survey	30 days	No
	Other in-hospital complication	Dichotomous	Survey	30 days	No

ASA, American Society of Anesthesiology; BL, baseline; CPAP, centre for preoperative assessment and planning; H&P, history and physical; METs, metabolic equivalents; NA, not applicable; ROS, review of systems.

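### The in-hospital complications model (Aim 2c) has no term for planned admission or surgery type, so part of the falls odds ratio may reflect case setting

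*Protocol article*

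**What the plan says.** The Analysis section defines the complications outcome as "Presence or absence of any complication that occurred in the hospital, as reported in the 30-day survey". It is any-versus-none per patient and is analysed by logistic regression.

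Every model contains age, sex, race, BMI and preoperative falls, together with "Charlson Comorbidity Index (≥3 vs <3), American Society of Anesthesiology (ASA) physical status (≥3 vs <3) and procedural cardiac risk". The complications model adds one outcome-specific confounder, smoking status. Leaving aside the exposure itself, that makes eight adjusters. Complications are also related to preoperative falls without adjustment, in the crude dose–response analysis and in hypothesis-generating χ² tests by complication subcategory.

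In-hospital falls appear once, under the Aim 1 descriptive statistics, as "Per cent who fell while still in the hospital". Table 1 types this variable as descriptive and takes it from V.3 of the 30-day survey only.

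On the data available, the article says that "Table 1 contains all variables to be collected for the study". No row gives planned admission status, admission or discharge date, or length of stay. Surgery type (10 categories, medical record) is listed, but the Analysis section uses it only to describe falls.

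On who is included, Study groups requires adulthood, English literacy, ability to consent and planned elective surgery, with no requirement of an overnight stay. Aim 2a speaks of "1 year following surgery of all types".

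The stated rule for choosing confounders is that "we selected confounding variables that are both routinely collected and known at the time of surgery planning".

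**The concern.** A complication in hospital needs a hospital stay in which to occur. The eligibility rules do not exclude same-day patients, and any who are enrolled have little opportunity for the outcome yet count fully in its denominator. If planned admission differs between prior fallers and non-fallers, the falls odds ratio takes up some of that difference even when falls carry no extra risk within either setting. The shift could go either way.

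The eight adjusters do not include case setting. ASA and Charlson, each split at 3, describe the patient and not the operation. Procedural cardiac risk is the closest proxy, but the Limitations section notes that the scored procedure is not always the one performed.

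For in-hospital falls the issue is narrower. A per cent of all surveyed patients mixes those who stayed with any who did not, and the reader cannot separate them.

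**Working it through.** **Inputs from the protocol (Sample size calculations, Analysis).** Complication rate 28%; prior fallers 26%; N = 7800; detectable increase 12% at 80% power and two-sided α = 0.05; minimum important difference 20% in proportions or ORs; analysis threshold α = 0.01.

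**Assumed inputs (not in the document).** Same-day or admitted shares by fall history, and the complication risk of same-day patients.

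**1. The plan's own figure.** Group sizes are 0.74 × 7800 = 5772 and 0.26 × 7800 = 2028. For 28% versus 28% × 1.12 = 31.36%, the pooled-variance normal approximation gives:
- SE under the null = √[0.2887 × 0.7113 × (1/5772 + 1/2028)] = 0.0117
- SE under the alternative = √[0.28 × 0.72/5772 + 0.3136 × 0.6864/2028] = 0.0119
- z = (0.0336 − 1.96 × 0.0117)/0.0119 ≈ 0.90, so power is 81.6%

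Reading 28% as the overall rate gives 79.9%. The stated 80% reproduces, so no figure in the plan is in error here.

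**2. Mixture with no falls effect within either setting.** Let s be a group's same-day share, c_d the same-day risk and c_i the inpatient risk. Then group risk = s·c_d + (1 − s)·c_i, with c_i solved so that the overall risk is 28%.

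Take same-day shares of 30% in non-fallers and 20% in fallers. The overall share is 0.74 × 0.30 + 0.26 × 0.20 = 0.274.
- c_d = 2%: c_i = (0.28 − 0.274 × 0.02)/0.726 = 0.378. Fallers 0.3065, non-fallers 0.2707. RR 1.13, OR 1.19.
- c_d = 10%: c_i = (0.28 − 0.0274)/0.726 = 0.348. Fallers 0.2984, non-fallers 0.2736. RR 1.09, OR 1.13.

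The same arithmetic gives:
- 30% versus 25% same-day: RR 1.05 to 1.07
- reverse gap, 20% versus 30%: RR 0.88 to 0.92
- equal shares: RR 1.00

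**3. A different set of assumptions.** Suppose 60% of non-fallers and 70% of fallers are admitted, and non-fallers' risk is 28%. Let k be ambulatory risk divided by inpatient risk, so c_i = 0.28/(0.6 + 0.4k).

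| k | c_i | Fallers' risk | RR | OR | Chance of crude p < 0.01 |
|---|---|---|---|---|---|
| 0 | 0.467 | 0.327 | 1.17 | 1.25 | 92% |
| 0.25 | 0.400 | 0.310 | 1.11 | 1.16 | 50% |
| 0.5 | 0.350 | 0.2975 | 1.06 | 1.09 | 14% |

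To produce a 12% increase from nothing, 67%, 71% or 79% of fallers would have to be admitted for k = 0, 0.25 or 0.5.

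All results in steps 2 and 3 are unadjusted. The existing covariates would remove a part that cannot be computed from the document.

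**4. In-hospital falls.** If 30% of patients were same-day and none of them fell in hospital, the per cent among admitted patients would be 1/(1 − 0.30) = 1.43 times the reported one.

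**The case against.** The strongest reply has five parts.

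- **The inferential result is adjusted.** The plan says its interest lies in regression ORs and not in crude comparisons, and age, ASA, Charlson and procedural cardiac risk plausibly track planned admission. This stands. It makes the figures above upper-end illustrations, not estimates of bias.
- **The inputs are assumed.** No passage gives a same-day share, a difference by fall history or a same-day complication rate. The survey wording is in supplements not shown, so how same-day patients answer the in-hospital items is unknown. This also stands.
- **The yardstick matters.** The 12% is what the sample can detect at α = 0.05; the effect the plan calls important is 20%. Every risk ratio above is below 1.20. Only the extreme case of zero ambulatory risk puts the OR past it (1.25).
- **Aim 2 is framed as prediction, where cumulative risk per patient is a proper target.** This is true of the crude association. But the plan also sets out to control confounding with variables available at planning, and planned admission would meet that rule where it is routinely recorded.
- **The Limitations section concedes that some confounders are unavailable.** It does so in general terms without naming admission, and surgery type is already in hand.

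Two stronger readings are tempting and not supported. A reader might infer that in-hospital falls will be compared by fall history; no such contrast is planned, and that item is purely descriptive. A reader might also infer that the model should adjust for length of stay; complications prolong the stay, so that would condition on a consequence of the outcome and would break the plan's own rule.

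**Conclusion.** The point holds as a minor one, confined to one secondary outcome and the denominator of one descriptive percentage. The omission is in the text: the variable list is presented as complete, admission is not required, and the complications model contains neither planned admission nor surgery type.

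Whether bias follows depends on planned admission differing by fall history after adjustment for the existing proxies. The document gives no means of judging that, so size and direction are unknown and the bias may be nil. Under the assumed 10-point gaps, the crude risk ratio with no true effect runs from about 1.06 to 1.13 when ambulatory risk is low to half the inpatient risk, and reaches 1.17 only if it is zero. That can be near the detectable 12% and is below the 20% minimum important difference on the risk-ratio scale. It would be wrong to conclude that case setting explains the whole association. The primary outcome, falls within 30 days, is not affected.

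**What to change.** Before analysis begins:

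1. Add planned same-day versus admitted status to the data request. The electronic medical record is already a source, though the article does not confirm that this field is held.
2. Add it to the complications model. If it cannot be obtained, add surgery type, which is already collected.
3. Repeat the complications model in admitted patients as a sensitivity analysis.
4. Report the in-hospital fall per cent among admitted patients as well as among all patients.
5. Do not adjust for actual length of stay.

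Cost: one extra field and one degree of freedom (nine for a 10-category surgery type), against about 0.28 × 7800 = 2184 events, plus one further model run. The admitted-only results would rest on fewer patients, for example 0.726 × 7800 ≈ 5,660 under the 30%/20% same-day assumption.

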## Limitations

This study contains several important limitations. First, the patients included in this study may represent a non-generalisable sample of the entire preoperative population. This study includes just one academic medical centre, and its patient population and rules for preoperative assessment clinic attendance may differ from that of other hospitals. In addition, only 65% of eligible preoperative assessment clinic attendees enrolled in the study, which may introduce bias. However, our analyses indicate that participants do not differ in important ways from non-participants. Furthermore, even if the sample was maximally biased, enrolling 65% of the actual target population means the results contain at least 80% accuracy.^28^ Another factor that biases the sample is non-response to the follow-up surveys. Although we mitigated non-response through an extensive follow-up protocol, only 55% of patients complete a 30-day survey.

The surveys also introduce several limitations. While the surveys are entitled ‘30-day’ and ‘1-year’ surveys, and most surveys occur near these times, the dates actually range from 20 to 120 and 275 to 455 days following surgery, respectively. In addition, each survey has two versions. Most questions are similar (readmissions) or identical (functional dependence, quality of life, complications) and can be combined. However, the postoperative falls question is significantly different. We will exclude results from the non-validated version, reducing the sample size available for this question. All important confounders will still be included, but the model may not have a sufficient number of outcomes to test all of the interactions of interest. Since many published papers do not test interactions, we do not think this compromises the robustness of the model.

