## Compliance

### Subject compliance

Since the exposure for this study is patient report of falls within the 6 months before surgery, no procedures for monitoring exposure compliance are necessary. Methods to improve completion of 30-day and 1-year surveys are described in the Data to be collected section.

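### The Aim 1 injury comparison sets 6 months of recall against about 30 days with no allowance for number of falls, which tends to make 30-day postoperative falls look less injurious

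*Protocol article*

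**What the plan says.** Under Aim 1, the Analysis section of the protocol article lists χ² tests, the first being "Proportion with any injury, comparing preoperative falls to postoperative falls at 30 days and 1 year". A second line repeats this for severe injury. They bear on the Aim 1 hypothesis in Specific aims: "We hypothesise that the occurrence, injuries and risk factors of postoperative falls will be similar to those of preoperative falls".

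Three other places in the article matter:

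- **Windows.** Subject compliance defines the exposure as "patient report of falls within the 6 months before surgery". The postoperative surveys are nominally at 30 days and 1 year, but Limitations says that "the dates actually range from 20 to 120 and 275 to 455 days following surgery, respectively".
- **Injury variable.** Table 1 lists "Fall-related injury" with the form "Check all that apply", collected at baseline, 30 days and 1 year. It lists no injury record for each fall.
- **Fall counts.** The same section plans to report "Number of falls (0, 1, 2, 3+) and fall rate in the 30 days and 1-year following surgery", so the number of falls per patient is available up to a cap of 3+.

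The Analysis section converts fall rates to a person-time scale. It says nothing comparable for the injury proportions, and it does not name their denominator.

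**The concern.** An any-injury indicator for a patient is the result of all that patient's falls in the window. Someone who fell three times has had three chances of injury, and someone who fell once has had one. A 6-month window holds more repeat fallers than a 30-day window, so the share of fallers with any injury is expected to be higher before surgery even if each fall is equally dangerous. The same holds for severe injury. A paired test would not cure this, because the proportions being compared would be the same.

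Two wrong conclusions are possible. If risk per fall is equal, the study may report that early postoperative falls are less injurious. If postoperative falls are in truth more injurious, the shorter window can hide it and appear to confirm the hypothesis of similarity.

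**Working it through.** **No stated figure to reproduce.** The article gives no calculation for the injury comparison. Its 26% and 10% can be checked through the primary-outcome power statement. With 1500 patients, 26% exposed (390 vs 1110), 10% falling overall, a 58% increase and two-sided α=0.05, power comes to 79.2% against the stated 80%. The inputs are therefore consistent.

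**Inputs from the article.** Fallers: 26% before surgery, 10% at 30 days and 28% at 1 year (validated question). About 1500 patients completed the 30-day version with that question. The significance threshold is 0.01.

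**Assumptions.** Injury risk per fall q = 30%, the same in every window. Fall counts are Poisson, or negative binomial with variance m + a·m² and a = 1, 2 or 4, with the same a in every window. The injury item covers the same period as the falls question. The two groups are treated as independent.

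**Step 1: mean falls per patient from the proportion of fallers F.**

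- Poisson: m = −ln(1 − F)
- Negative binomial: m = [(1 − F)^(−a) − 1]/a

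**Step 2: share of fallers with any injury.**

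- Poisson: [1 − exp(−q·m)]/F
- Negative binomial: [1 − (1 + a·q·m)^(−1/a)]/F

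Example with a = 1. Before surgery, m = 1/0.74 − 1 = 0.351, and the share is [1 − 1/1.1054]/0.26 = 36.7%. At 30 days, m = 1/0.90 − 1 = 0.111, and the share is [1 − 1/1.0333]/0.10 = 32.3%.

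**Step 3: chance of p<0.01 with 390 vs 150 fallers** (0.26 × 1500 and 0.10 × 1500), by the two-proportion test with pooled variance under the null. For a = 1 the difference is 0.044, the pooled SE 0.0460 and the unpooled SE 0.0453. Then (0.044 − 2.576 × 0.0460)/0.0453 ≈ −1.64, which gives about 5%.

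| Counts | Preoperative | 30 days | Relative deficit | Chance of p<0.01 |
|---|---|---|---|---|
| Poisson | 33% | 31% | 6% | 2% |
| a = 1 | 37% | 32% | 12% | 5% |
| a = 2 | 40% | 33% | 17% | 13% |
| a = 4 | 48% | 36% | 25% | 47% |

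The nominal rate is 1%. Only the last row's deficit exceeds the 20% minimum important difference that the article sets for proportions. Repeating the steps with q = 20% and 40% gives about 2% (Poisson), 4-6% (a = 1), 10-15% (a = 2) and 40-47% (a = 4), so dispersion matters far more than q.

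**Step 4: 1 year.** For a = 1, 2 and 4 the shares are 37% vs 37%, 40% vs 41% and 48% vs 50% (preoperative vs 1 year). Taking 1500 patients at 1 year as well (an assumption, giving 0.28 × 1500 = 420 fallers), the chance of p<0.01 is 1-2%.

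**Step 5: if all patients are the denominator.** With an assumed equal 40% of fallers injured, the proportions are 0.26 × 40% = 10.4%, 0.10 × 40% = 4.0% and 0.28 × 40% = 11.2%. At 1500 per time point, p<0.01 is almost certain for 10.4% vs 4.0%. That difference reflects how many patients fell in each window, not how injurious the falls were.

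**The case against.** The size rests on two quantities that the article does not give: injury risk per fall and count dispersion. With Poisson counts the gap is about 2 points and the error rate barely above nominal. Only strong clustering of falls makes it large. This stands, and it is why a range is shown.

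The injury item's wording is in supplementary surveys that are not shown. If it asked about each fall separately, the mechanism would disappear. Table 1 suggests otherwise, but this remains an inference. Surveys returned as late as 120 days may also bring some postoperative windows closer to 6 months. The calculation works from the proportion of fallers rather than from days, so it does not depend on an exact 30-day window.

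An article may leave a denominator to a fuller plan. But this article itself fixes the test and the contrast, so the point concerns a stated analysis and not an absent detail.

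Three stronger readings are tempting and not supported:

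- **That both contrasts are distorted.** Among fallers, the protocol's own 26% and 28% leave the 6-month versus 1-year contrast almost unaffected. A larger 1-year shift appears if a constant fall rate is assumed, but that predicts 36-45% fallers at 1 year, not 28%.
- **That false rejection reaches 16%, 31% and 71%** (a = 1, 2, 4). Those are rates at α=0.05; the article sets 0.01.
- **That a false difference is near certain.** This holds only with all patients as denominator, which fits poorly with a comparison of preoperative falls to postoperative falls.

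**Conclusion.** The point holds for the 30-day contrast. If the direction is to reverse, falls would have to cluster in fewer patients after surgery than before; with similar clustering it follows from one injury item per survey and more falls per faller in 6 months. The size is uncertain: a spurious deficit of about 2 to 12 percentage points at an assumed 30% risk per fall. The tests belong to a descriptive aim and bear on neither the primary outcome nor the Aim 2 models. The change is worth making because the article ties these tests to a stated hypothesis.

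**What to change.** - State that the denominator is patients who reported at least one fall in the window.
- Compare any injury and severe injury with adjustment for, or stratification by, number of falls (1, 2, 3+).
- Give the comparison among patients with exactly one fall as a sensitivity analysis.
- Report the unadjusted proportions beside their recall windows as description only, without a test of similarity.

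This uses counts already collected and changes one part of the analysis. The costs are wider intervals and some remaining confounding. Under the negative-binomial assumptions above, 77-90% of 30-day fallers (about 116-135 of 150) and 50-74% of preoperative fallers (about 194-289 of 390) would have fallen exactly once. Counts capped at 3+ prevent full adjustment. A patient with one fall in 30 days also has a higher underlying fall rate, on average, than one with a single fall in 6 months, and may differ in frailty. That limit should be stated with the result.
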